## Abstract

**Background:**

We describe the rationale and protocol for a randomized controlled trial (RCT) to assess whether intrauterine contraception placed immediately after a second trimester abortion will result in fewer pregnancies than current recommended practice of intended placement at 4 weeks post-abortion. Decision analysis suggests the novel strategy could substantially reduce subsequent unintended pregnancies and abortions. This paper highlights considerations of design, implementation and evaluation of a trial expected to provide rigorous evidence for appropriate insertion timing and health economics of intrauterine contraception after second trimester abortion.

**Methods/Design:**

Consenting women choosing to use intrauterine contraception after abortion for a pregnancy of 12 to 24 weeks will be randomized to insertion timing groups either immediately (experimental intervention) or four weeks (recommended care) post abortion. Primary outcome measure is pregnancy rate at one year. Secondary outcomes include: cumulative pregnancy rates over five year follow-up period, comprehensive health economic analyses comparing immediate and delayed insertion groups, and device retention rates, complication rates (infection, expulsion) and, contraceptive method satisfaction. Web-based Contraception Satisfaction Questionnaires, clinical records and British Columbia linked health databases will be used to assess primary and secondary outcomes. Enrolment at all clinics in the province performing second trimester abortions began in May 2010 and is expected to complete in late 2011. Data on one year outcomes will be available for analysis in 2014.

**Discussion:**

The RCT design combined with access to clinical records at all provincial abortion clinics, and to information in provincial single-payer linked administrative health databases, birth registry and hospital records, offers a unique opportunity to evaluate such an approach by determining pregnancy rate at one through five years among enrolled women. We highlight considerations of design, implementation and evaluation of a trial expected to provide rigorous evidence for appropriate insertion timing and health economics of intrauterine contraception after second trimester abortion.

**Trial registration:**

Current Controlled Trials ISRCTN19506752

## Introduction

Abortion is common in Canada with 96,815 reported in 2005 [1]. Canadian women seeking abortion represent a high risk group for recurrent unintended pregnancy as 38% have had at least one previous abortion [2]. About 12% of all abortions occur past the 12th week in pregnancy (second trimester)[3,4]. Women seeking abortion in the second trimester are disproportionately from marginalized and vulnerable populations [3-6], and recurrent unintended pregnancies may further exacerbate social and economic disadvantages [7]. The most effective contraceptive is "forgettable"[8], that is: a method requiring user attention no more often than every 3 years. Intrauterine contraception (IUC) is efficacious, and thus highly effective contraception [9-12]. Robust evidence exists to favour immediate insertion of an IUC after first trimester abortion [13-19] and post-partum [20-23].

To minimize expulsion and potential for perforation of the IUC device, current recommended care and product monographs indicate delaying insertion after a second trimester abortion until substantial uterine involution (return to non-pregnant size): typically 4-6 weeks [24,25]. This recommendation appears to be founded upon a theoretical risk of greater rates for expulsion prior to uterine involution, as we were unable to find published evidence to support this assertion. Although the rates for both expulsion and perforation are believed to be only marginally higher than for insertion at 4 weeks [26,27], as few as 26% of women return by 6 weeks for a planned delayed insertion [28].

British Columbia (BC) administrative health databases track health care services provided within a single-payer universal health care system. These databases enable a linkage of study participant information to health system data on all births, abortions, miscarriages, any pregnancy related visits, hospital admissions and prescriptions dispensed following study enrollment. This method can substantially reduce attrition rate in a population known to have low post abortion follow up adherence [27-31].

The proposed randomized controlled trial (RCT) of immediate compared to a planned delayed device insertion following second trimester abortion is the first to examine both the levonorgestrel and the copper device and the first to report on pregnancy rate at one year as the primary outcome measure. The study will provide generalizable results using an intention-to-treat framework for the hypothesis: *Intrauterine contraception placed immediately after a second trimester abortion will result in fewer pregnancies than current recommended care of intended placement at 4 weeks post-abortion*. The health economic analysis of costs and cost-effectiveness will facilitate determination of population health implications to inform health systems and health care delivery decisions.

## Methods

### Study design

Women having a second trimester abortion at any BC abortion clinic, and choosing an IUC for post-abortion contraception will be eligible to participate in the study. Consenting participants choose either a copper or a levonorgestrel-releasing IUC and are then randomly allocated to an insertion time immediately or four weeks after their abortion. Contraception Satisfaction Questionnaires (CSQ), clinical records and the linked provincial health administrative databases will be accessed to determine all pregnancies occurring within one year of enrollment, supplemented with a variety of secondary outcomes.

### Sample Size and Power Calculations

350 women choosing a levonorgestrel-releasing IUC (LNG-IUC, "Mirena^®^", Bayer Inc, Canada), and 366 women choosing a "T" shaped copper IUC with 380 mm^2 ^surface area of copper including copper bands on the "T" arms (CuT380-IUC, "Flexi-T380(+)^®^", Prosan, The Netherlands) will be recruited and randomly allocated to each of two treatment arms: immediate insertion (experimental intervention) vs. planned delayed insertion (recommended care), representing a total enrollment of 716 women into this Phase IIIb RCT (See Table 1). This sample size will provide 90% power in the levonorgestrel stratum to distinguish predicted one year pregnancy rates of 1.2% (immediate) versus 8.7% (delayed) and 80% power for corresponding detection of 2.7% and 9.7% in the copper device users.

**Table 1 T1:** Enrollment Allocation

	Immediate	Delayed	Total
LNG-IUC	175	175	350

CuT380-IUC	183	183	366

Total	358	358	716

### Estimation of Probable Rates of Pregnancy

The pregnancy rates used in our sample size calculation are justified as follows. The one year failure rate of the LNG-IUC device is known to be 0.1%[32] except in the case of spontaneous expulsion that we conservatively estimate occurs when immediately inserted after second trimester abortion with a probability of 0.05 (observed rate 0.03 by Drey [27] and Cremer [29]). Our estimated post-abortion pregnancy probability in the absence of an IUC is 0.24 [33]. Therefore the estimated pregnancy rate in the immediate insertion LNG-IUC group is expected to be:

In the delayed group, we conservatively estimate 65% of women will return for insertion of the IUC (Stanek found 26% return for planned delayed insertion [28], and Cremer 30%[29]), and we assume (conservatively) the high expulsion rate of the immediate insertion group. These assumptions imply a one-year pregnancy rate of

The one year failure rate for the CuT380-IUC is 1.7%[34]. Using the above formula this yields rates for immediate and delayed insertion of .028 and .102 respectively. Allowing for a loss to follow-up of up to 5% provides conservative estimates of the observed pregnancy rates of .012 and .0874 in the LNG-IUC cohort and .027 and .097 in the CuT380-IUC group.

### Inclusion Criteria

All women at participating study sites who have completed informed consent for an abortion over 12 and under 24 weeks gestational age (as determined by ultrasound), who are residents of BC enrolled in the universal provincial medical services plan and have chosen to use an IUC for post-abortion contraception are eligible to participate.

### Exclusion Criteria

Women are not eligible if they intend to move from BC within the next year or if they intend to conceive within one year. In addition, if they have a contraindication to the use of the IUC they have chosen (see Table 2) or are currently enrolled in another clinical trial they will be excluded. Post randomization exclusion factors include perforation or excessive bleeding at the time of their abortion or uterine anomaly detected at the time of the abortion procedure. These exclusions are designed to be only those which, in real life, would preclude a woman from being able to choose this method of contraception. This study has no minimum age criteria for enrollment.

**Table 2 T2:** Inclusion and Exclusion Criteria

*Inclusion Criteria - This study will be offered to women at the study sites who meet all of the following criteria: *
Have completed informed consent for an abortion over 12 and under 24 weeks gestational age.
Have chosen an IUC (either LNG-IUC or CuT380-IUC) for contraception post abortion.
Are residents of British Columbia registered with the Medical Services Plan health care system.

Exclusion Criteria

Intention to move from BC within the next year
Intention to conceive within the next year
Uterine cavity anomalies causing distortion of the endometrial canal including fibroids of more than 5 cm, excluding repaired uterine septum
Current untreated PID, Chlamydia, gonorrhea, cervicitis or lower genital tract infection (recent infection is not a contraindication to IUC insertion[35])
Wilson's Disease (if choosing a CuT380-IUC)
Undiagnosed abnormal uterine bleeding
Known uterine or cervical malignancy or cervical dysplasia
Known or suspected progestin-dependent neoplasia, including breast cancer (if choosing a LNG-IUC)
Active liver disease or dysfunction (if choosing a LNG-IUC)
Actual benign or malignant liver tumours (if choosing a LNG-IUC)
Hypersensitivity to levonorgestrel or any of the other ingredients in the formulation or component of the container components of Mirena^® ^(if choosing a LNG-IUC)
Bacterial endocarditis
Established immunodeficiency (HIV positivity is not an exclusion unless immunodeficient)
Acute malignancies affecting blood or leukemias
Recent trophoblastic disease while hCG levels are elevated
Currently enrolled in another investigational study

Post Randomization Exclusion Criteria

Failure to undergo an abortion (ie: participants who elect to continue their index pregnancy at any time subsequent to randomization)
Uterine perforation at the time of abortion

Bleeding of more than 500 cc during abortion

Uterine cavity anomalies as outlined above

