### Immediate insertion group protocol

Women randomized to immediate insertion have their chosen IUC inserted by their surgeon immediately following the abortion prior to leaving the procedure or operating room. As per standard clinic protocols all women in both groups have polymerase chain reaction (PCR) testing for chlamydia and gonorrhoea prior to their abortion, and receive two grams metronidazole single observed dose as prophylaxis against postoperative infection [38]. Women deemed to be at higher risk of a sexually transmitted infection (as per criteria used by all BC clinics [38]), and those with positive PCR results, receive one gram of azithromycin as well. An ultrasound image of the IUC in situ is recorded. If an ultrasound machine is not immediately available in the operating room, arrangements are made for an ultrasound to be performed to confirm proper IUC position.

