### Delayed insertion group protocol

Women randomized to planned delayed insertion are managed as closely as possible to standard practice. Participants are asked to make an appointment for follow-up and IUC insertion at 4 +/-1 weeks after the date of their abortion. All women are offered one month of an alternate contraceptive. An opportunity to return for follow-up and IUC insertion at any study clinic is available to all women, as per recommended post abortion delayed IUC insertion practice. Participants who have travelled over 100 km from a study clinic are asked to make arrangements for insertion in their home community. Study participants experience conditions as close to standard non-study delayed insertion conditions as possible. These women receive a "SmartPayment"^® ^card [39] and a prescription for the IUC. This permits participants to receive the IUC cost-free (as is the case for those able to return to the study clinic for insertion) and for the patient's pharmacy of choice to be reimbursed for the IUC. The participant is also given a requisition for a post-insertion ultrasound. The BC Medical Services Plan provides payment for the IUC insertion and the post-insertion ultrasound. This procedure is designed to as closely as possible emulate the real-life conditions each participant would experience were she not in a research study. This process eliminates possible bias in IUC insertion rate, and thus pregnancy rate, were she to take home a free study IUC or we to courier it to her designated health care provider.

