### Analysis

*Primary outcome *will be examined in an intention-to-treat framework as pregnancy rate at one year among women randomized to immediate insertion compared to women randomized to a planned insertion at 4 weeks ("delayed insertion") for each of the two IUC devices. For example, if women in the delayed group present for insertion after the specified 4+/-1 week insertion window, or even at the time of a subsequent abortion or delivery, we will insert the device at the women's request and her assignment for the primary analysis will not change. Similarly if for any reason a woman assigned to the immediate insertion group is unable to have her insertion immediately (for example, should she have an unattended expulsion/delivery of her pregnancy prior to the planned surgical abortion) then insertion will be offered at the time the woman and her physician would normally undertake to do so, and whether or not her insertion ever occurs, her assignment for the purpose of analysis will not change. Thus our primary outcome of pregnancy rate at one year reflects real life conditions.

*Secondary outcomes *include: costs and cost effectiveness, cumulative annual pregnancy rate, device insertion rate, loss to follow-up; continuation of method; adverse events (such as infection or perforation); expulsion; outcomes among those participants who were chlamydia positive at the time of insertion; satisfaction with IUC chosen and with insertion timing assigned. These outcomes will be assessed initially at one year, then annually through the five year device effectiveness period.

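### Perforation is a safety outcome and also a post-randomisation exclusion worded by timing alone, so a perforation arising or first seen at immediate insertion could be lost from one arm's count

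*Protocol article*

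**What the plan says.** Four parts of the protocol article bear on this.

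- **Outcome.** The Analysis section lists among the secondary outcomes "adverse events (such as infection or perforation", together with expulsion and others. The Introduction shows why perforation matters here: "To minimize expulsion and potential for perforation of the IUC device, current recommended care and product monographs indicate delaying insertion".
- **Exclusion.** The Exclusion Criteria text says "Post randomization exclusion factors include perforation or excessive bleeding at the time of their abortion", and the post-randomisation part of Table 2 has the item "Uterine perforation at the time of abortion". Neither names a cause or says that the perforation must precede insertion. The text adds a purpose: "These exclusions are designed to be only those which, in real life, would preclude a woman from being able to choose this method of contraception".
- **Immediate arm.** The device is "inserted by their surgeon immediately following the abortion prior to leaving the procedure or operating room".
- **Delayed arm.** Women are asked to book "IUC insertion at 4 +/-1 weeks after the date of their abortion". Those who travelled more than 100 km are asked to arrange insertion in their home community.

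The article states intention-to-treat for the primary outcome. It does not say whether a woman excluded after randomisation still contributes to the adverse-event counts.

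**The concern.** The same kind of event is both something the trial means to count and a reason to remove a randomised woman. That would be harmless if the removal rule could act equally on both arms, and for perforations made by the abortion itself it does. For insertion perforations it does not, because the window described as the time of the abortion overlaps with device insertion in the immediate arm only.

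Within one session, a surgeon may be unable to tell whether a perforation found on placing the device was made by the device or a few minutes earlier by the abortion instruments. The surgeon who makes that call has just inserted the device and so knows the allocation. If the call is the abortion, the exclusion applies and the event may leave the count with the woman.

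At stake is the comparison of perforation between arms. Perforation is one of the two risks the article gives as the reason for current advice to delay, and the trial is meant to inform that advice. The problem is separate from any effect of the exclusions on pregnancy rates and would remain if those rates were unbiased.

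**Working it through.** **Step 1: which events can the exclusion reach?** Setting the sections side by side:

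| Perforation | Immediate arm | Delayed arm |
|---|---|---|
| Made by the abortion and recognised before any insertion | Excluded | Excluded |
| Clearly made by insertion | Kept on the likely reading | Kept |
| First recognised at insertion, cause uncertain | No rule; may be excluded | Out of reach of the exclusion, since insertion is weeks later |

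Only the third row differs by arm, and only there does the outcome depend on a judgement made with knowledge of the allocation.

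**Step 2: how many events are involved?** The article has no perforation rate, so there is no figure of its own to reproduce. The sample-size figures for pregnancy do not bear on the point.

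Inputs:
- Women per arm: 175 + 183 = 358 (Table 1).
- Share of the delayed arm returning for insertion: 65% (Estimation of Probable Rates of Pregnancy), giving 0.65 × 358 = 232.7, about 233 insertions.
- Perforation risk per insertion, *q*: **assumed** 0.1%, 0.5% or 1%, equal in both arms.
- Share *f* of immediate-arm insertion perforations attributed to the abortion: **assumed** 0, one half or all.

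Formulas: immediate-arm count = 358 × *q* × (1 − *f*); delayed-arm count = 232.7 × *q*.

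| *q* | Immediate, *f* = 0 | Immediate, *f* = 0.5 | Immediate, *f* = 1 | Delayed |
|---|---|---|---|---|
| 0.1% | 0.36 | 0.18 | 0 | 0.23 |
| 0.5% | 1.79 | 0.90 | 0 | 1.16 |
| 1% | 3.58 | 1.79 | 0 | 2.33 |

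Taking all 358 immediate-arm women as having an insertion is a slight overcount, since some will be excluded or not have the device placed.

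**Step 3: reading the table.** At equal risk the immediate arm should show more events, because more of its women have an insertion: 358*q* − 232.7*q* = 125.3*q*, or 0.13 to 1.25 events. That excess vanishes when 358(1 − *f*) = 232.7, that is, when *f* = 1 − 0.65 = 0.35. Above that share the expected count is lower in the immediate arm. Per insertion, the apparent risk ratio is 1 − *f*, whatever *q* is. The direction therefore does not depend on the assumed risk; the size depends entirely on *q* and *f*.

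**The case against.** The strongest reply is that the article does separate the abortion from the insertion. Insertion comes "immediately following the abortion prior to leaving the procedure or operating room", so after it. The neighbouring Table 2 item confines bleeding to the abortion itself. The purpose sentence describes conditions that would rule out the method, which fits something present before placement and not an injury made by placing the chosen device. Analysis methods counts secondary events in the year following the abortion, and insertion too follows it. I accept this as the likely intent. On that reading a clear insertion perforation is kept, and a loss requires misattribution as well.

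Other points also stand:
- The position ultrasound may be arranged for later, and a perforation first seen then is not obviously at the time of the abortion.
- Billing, procedure codes and follow-up records supplement the surgeon's account.
- Perforation is only an example in the adverse-event list, and the Abstract names infection and expulsion as complications without it.
- With so few expected events, the trial can say little about perforation under any rule.

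A reader might infer that the rule empties the immediate-arm count while delayed-arm perforations are always counted. The article supports neither. The first needs every insertion perforation to be misattributed. The second overlooks that some delayed insertions take place in the home community, where detection is not assured. Nor is there ground for assuming a doubled risk with immediate insertion, since the Introduction says the rates are believed to be only marginally higher.

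What the reply does not do is classify a perforation first recognised at insertion, or say that excluded women stay in the safety count. An analysis plan would inherit this fixed exclusion along with the outcome it overlaps.

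**Conclusion.** The point holds in a limited form. The exclusion is worded by timing, and in one arm only that timing overlaps with the procedure whose safety is being compared. This opens the way to a one-sided loss of events, in the direction that favours immediate insertion. It is a possible bias, not a demonstrated one: it requires that some same-session perforations be attributed to the abortion and that excluded women be left out of the adverse-event count.

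Under an assumed risk of 0.1% to 1% per insertion, about 0.4 to 3.6 immediate-arm events are open to misclassification, against about 0.2 to 2.3 delayed-arm events at equal risk that the exclusion cannot reach. The effect on the primary pregnancy outcome is negligible. Importance is modest, but in a comparison with so few events one or two lost cases can change what is reported, and the remedy is nearly free.

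**What to change.** 1. **Safety analysis.** Count every uterine perforation from the start of the abortion procedure onward, whatever its suspected cause, in all randomised women who had the procedure, by assigned arm and regardless of the Table 2 exclusions. Also report separately those recognised before the insertion attempt and those recognised at or after it.
2. **Exclusion wording.** State that, for analysis, the Table 2 item covers only perforation recognised before any insertion attempt, so that the Exclusion Criteria agree with the immediate-insertion section and the outcome list. Record that timing on the procedure form.

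This concerns counting only; clinical management after a perforation is unchanged.

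The cost is about one sentence in the Analysis section, one in Table 2 and one item on the form, with no extra patients or procedures. The downside is added noise: abortion perforations enter both arms and are balanced only in expectation. The article gives no background rate from which to size that noise, which is why the split by timing of recognition should be reported alongside the total.
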